### Intervention plan

#### Dosage, route of administration, and period of investigational drugs

In accordance with the package insert, and as in a previous study [9], the first oral dose of celecoxib will be 400 mg, followed by 200 mg in both the celecoxib and control groups. Patients in the celecoxib group will receive 400 mg celecoxib 2 hours after TKA, followed 6 hours later by 200 mg celecoxib and 200 mg celecoxib twice daily beginning the day after surgery until day 7. Patients in the control group will receive 400 mg celecoxib on the morning of the second day after surgery, which is the day of PCA fentanyl removal, followed 6 hours later by 200 mg celecoxib and 200 mg twice daily until the seventh day after surgery [9].

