### Outcomes

#### Primary outcome measure

The primary outcome measure in this study will be patient-reported VAS pain score at 9 o’clock on the second day after TKA. This measure will allows us to identify the effect of early administration of celecoxib (Table 1).

**Table 1 Tab1:** Data collection schedule

	Day before surgery	Day of surgery	Postoperative day(s)				Discontinuance
			1	2	3–6	7	
VAS pain score	●	●^a^	●^b^	●^b^	●^b^	●^b^	●
Fentanyl consumption		●	●	●			
ROM	●			●		●	●
VAS sleep score^c^	●	●	●	●		●	●
SLEEPSCAN™ %	●	●	●	●		●	●
Patient satisfaction						●	●
Evaluation by physician						●	●
PONV		●	●	●	●	●	●
Rescue consumption				●	●	●	●
Adverse events		●	●	●	●	●	●

^a^Two hours after the end of surgery; ^b^9 a.m. before oral administration; ^c^evaluation the next day; % overnight measurement

Abbreviations: VAS visual analog scale; ROM range of motion of the knee; PONV postoperative nausea and vomiting

SLEEPSCAN™ (TANITA Corporation, Japan) is a tool for evaluating sleep quality

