#### Secondary outcome measures

For secondary outcome measures, fentanyl consumption through PCA is assessed at 2 days after surgery; VAS pain score is assessed at 9 a.m. each day from 1 to 7 days after surgery; range of motion of the knee joint is assessed at 9 a.m. at 2 and 7 days after surgery; postoperative sleep quality is evaluated at 1, 2 and 7 days; overall patient satisfaction during the period of medication is evaluated at 7 days after surgery; overall evaluation by the physician during the period of medication is assessed at 7 days after surgery; incidence rates of postoperative nausea and vomiting and frequency of taking anti-nausea pills is assessed for the 7 days after surgery; and consumption of rescue analgesics (diclofenac sodium suppositories) after the discontinuation of PCA fentanyl is assessed overall for the 7 days after surgery (Table 1).

Sleep quality at 9 a.m. on postoperative 1, 2 and 7 days will be evaluated by patient-reported VAS sleep disturbance. For objective sleep assessment, sleep latency, sleep efficacy, nocturnal awakening, depth of sleep, body motion, and deep sleep time will be monitored by SLEEPSCAN™ (TANITA Corporation, Japan) [11]. SLEEPSCAN monitors body motion, breathing, and heart rate through the bedding mattress with a water seal and pressure sensor, without the necessity of installing direct sensors, including bioelectrodes, on the human body [11].

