#### Sample size calculation

The primary outcome of this study is patient-reported VAS pain score on the second day after surgery, based on the hypothesis that immediate postoperative administration of oral celecoxib could reduce patient-reported VAS pain score 48 hours after TKA surgery compared with the control group.

Sample sizes are chosen to detect clinically relevant differences using a power analysis based on previously published data evaluating the effect of celecoxib on VAS pain score after TKA [9]. The minimal clinical significance in VAS pain score was defined as the mean difference between current and preceding scores when the subject reported “a little worse” or “a little better” pain [12]. Previous study shows that VAS pain scores 48 hours after TKA surgery were reported to be 21.3 ± 16.8 mm in patients receiving celecoxib plus PCA morphine and 34.3 ± 16.6 mm in patients receiving PCA morphine alone [9]. Based on these findings, we hypothesized that VAS pain score 48 hours after surgery will be 22 mm for the celecoxib group (postoperative oral celecoxib plus nerve block and PCA fentanyl) and 33 mm for the control group (nerve block and PCA fentanyl alone), with a standard deviation set at 20.0 mm and a ratio of patients in the celecoxib to the control group of 1:1. Calculations showed that a sample size of 53 patients per group would provide 80 % power (alpha = 0.05, two-tail) to detect a difference in VAS pain score between the two groups after treatment, and also the minimal detectable change of 10 mm within each group [9]. Assuming a 10 % dropout rate, 60 patients per group, or a total of 120 patients, are required.

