### Plan for statistical analysis

The intention-to-treat analysis will be conducted for all patients who underwent randomization. Baseline information on study subjects in two treatment groups such as demographics, preoperative VAS pain scores, ranged of motion and sleep quality will be described. The primary outcome that the differences of VAS pain scores between celecoxib and control groups at the second day after surgery will be analyzed by ANOVA. The secondary outcomes including the pain-medication use, adverse reactions, VAS pain scores, range of motion of knee joint, sleep quality, patient satisfaction, and overall evaluation by physicians after surgery will be analyzed by ANOVA or Chi square test. Nonparametric tests may be used for continuous variables if they are not normally distributed. Between-group comparisons of treatment effect for primary and secondary outcomes, except for pain-medication use and adverse events, will also be conducted with the use of a mixed-effects model, with patient as a random effect and time of assessment (baseline and follow-up days), study group, and baseline values of the outcome as fixed effects.

Significance will be set as *P* < 0.05. All statistical analyses will be performed by using SAS 9.4 (SAS Institute Inc., Cary, NC, USA).

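### The supplementary mixed model has no group-by-time term and uses baseline as both response and covariate, so its group coefficient does not estimate the day-2 effect

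*Protocol article*

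**What the plan says.** The primary outcome is a single time point, the "patient-reported VAS pain score at 9 o’clock on the second day after TKA" (Primary outcome measure). Under Plan for statistical analysis, the between-group difference on that day is tested by ANOVA. Secondary outcomes, including patient satisfaction and the physician's evaluation, go to ANOVA or a chi-square test.

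The same section then adds a mixed-effects model for comparing the groups on primary and secondary outcomes, leaving out only pain-medication use and adverse events. Patient is the random effect. The fixed effects are given as "time of assessment (baseline and follow-up days), study group, and baseline values of the outcome as fixed effects". No interaction appears in the list.

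Two other sections bear on this. On dosing: "Patients in the control group will receive 400 mg celecoxib on the morning of the second day after surgery". Table 1 notes that the morning VAS is recorded before the oral dose. On the timing of one secondary outcome: "overall patient satisfaction during the period of medication is evaluated at 7 days after surgery". Table 1 schedules patient satisfaction and physician evaluation only at day 7 or at discontinuance, with no baseline value.

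**The concern.** A model with group and time as main effects only assumes the same treatment difference at every assessment. The design makes that hard to defend. The control arm starts celecoxib just after the day-2 score, so only days 1 and 2 compare celecoxib with none. Days 3-7 compare early with delayed celecoxib.

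The baseline row adds a second distortion. There the response and the covariate are the same number, so the row carries no information on treatment and only pulls the coefficient toward zero.

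The model is nevertheless put forward as a between-group comparison for the primary outcome, at the same P < 0.05. The report could then give two treatment effects for day-2 pain that measure different things, with no rule for which to believe. The mixed model is also the only listed analysis that adjusts for baseline, so some readers may prefer it.

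For the two outcomes measured once, the model cannot be fitted as described: there is no baseline covariate, and a patient effect cannot be separated from residual error with one value per patient.

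**Working it through.** **Inputs from the protocol (Sample size calculation).** Means are "22 mm for the celecoxib group" and "33 mm for the control group", so the difference is 33 − 22 = 11 mm. The "standard deviation set at 20.0 mm" applies, with 53 per group, two-sided alpha 0.05 and 80% power. VAS is scored the day before surgery and at 9 a.m. on days 1-7. Table 1 also shows a score two hours after surgery.

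**Assumptions not in the protocol.** The effect is 11 mm on days 1 and 2. The effect d on each of days 3-7 is varied. Within-patient correlation ρ is the same for every pair of times. Data are complete.

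**1. The plan's own figure.** Standard error of the day-2 difference = 20 × √(2/53) = 3.885 mm. The noncentral t distribution gives power 0.801 at 53 per group and 0.793 at 52. The stated 53 is reproduced.

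**2. What the group coefficient estimates.** With complete data and a random patient intercept, the coefficient is the baseline-adjusted group difference in each patient's mean over all response rows. With eight rows:

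patient mean = (baseline + 7 × mean of days 1-7) / 8.

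After adjustment for baseline the first term contributes nothing, so

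coefficient = (7/8) × average effect over days 1-7 = (11 + 11 + 5d) / 8.

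If the two-hour score is also a response, with zero effect because the first dose is only then due, the divisor is 9.

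| Effect on days 3-7 | Sum over days 1-7 (mm) | 8 rows (mm) | 9 rows (mm) |
|---|---|---|---|
| none | 22 | 2.75 | 2.44 |
| fading 8, 6, 4, 2, 0 mm | 42 | 5.25 | 4.67 |
| half (5.5 mm) | 49.5 | 6.19 | 5.50 |
| constant 11 mm | 77 | 9.63 | 8.56 |

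Simulation on eight rows (2000 trials per scenario, ρ from 0.3 to 0.7) gave means of about 2.7, 5.2, 6.2 and 9.6 mm. A fitted mixed model gave 2.7 and 9.6 mm in the two extreme cases. The coefficient would equal 11 mm only if (22 + 5d)/8 = 11, that is d = 13.2 mm, a later effect larger than the day-2 effect.

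**3. Separating the two faults.** Dropping only the baseline row multiplies the estimate by 8/7 (2.75 to 3.14 mm; 9.63 to 11.0 mm). The standard error changes by the same factor: in the fitted models at ρ = 0.5 and constant effect, 1.926 becomes 2.201 mm, and 1.926 × 8/7 = 2.201. The test and its power do not change. The larger error comes from averaging over days 3-7 with no interaction.

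**4. Power of the group test as written.** The variance of a patient's days 1-7 mean given baseline is 20² × [(1 + 6ρ)/7 − ρ²]. At ρ = 0.4 this is 400 × (0.4857 − 0.16) = 130.3, and the standard error is √(130.3 × 2/53) = 2.217 mm. By the noncentral t with 103 degrees of freedom:

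| d (mm) | Average effect, days 1-7 (mm) | Power |
|---|---|---|
| 0 | 22/7 = 3.14 | 0.29 |
| 3 | 37/7 = 5.29 | 0.66 |
| 5 | 47/7 = 6.71 | 0.85 |
| 11 | 77/7 = 11.0 | above 0.99 |

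The day-2 ANOVA has 0.80. At this correlation the two are equal near d = 4.4 mm (average 44/7 = 6.29 mm, power 0.80). With no effect after day 2, simulated power was 0.28-0.35 over ρ = 0.3-0.7.

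**5. After correction.** With follow-up rows only and group-by-time added, the fitted day-2 contrast averaged 10.7 to 11.0 mm (standard error about 3.4 mm, ρ = 0.5, 40 runs per scenario). The 11 mm effect is recovered.

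**The case against.** The strongest reply is that this is not the primary analysis. ANOVA on day 2 is named first, the sample size is built on it, and the mixed model is an addition. That stands, and it sets the severity: whatever the mixed model shows, the day-2 effect is still estimated directly with the planned power.

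A reader might infer that the model's result is unrelated to the day-2 effect, or that it must lose power. The documents support neither. Day 2 is one of the averaged occasions. The protocol's rationale, less sensitization and immediate dosing better than delayed, allows for a benefit lasting beyond day 2. If the effect lasts, averaging raises power. A reader might also take about 22% of the true effect (2.44/11) as the expected result. That figure needs both no effect after day 2 and the two-hour score as a response, and the model text names only baseline and follow-up days.

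The problem for single-assessment outcomes is also mild. Single-time tests are already planned for them, and a model that cannot be fitted gives no misleading result.

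Finally, an analysis plan might add an interaction. That would be a good answer had the article left the model open, but it gives an explicit list of fixed effects.

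**Conclusion.** The point holds for the supplementary model: as specified, its group coefficient does not estimate the effect that defines the primary outcome. For a day-2 effect of 11 mm it would report between 2.75 and 9.63 mm on eight rows, or 2.44 to 8.56 mm if the two-hour score is included. Where it falls depends on the unstated effect on days 3-7, and the range rests on complete data and 11 mm on both days 1 and 2. The missing interaction is the main fault. The baseline row alone costs one eighth of the estimate and leaves the P value unchanged.

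Loss of power is conditional on the effect fading after day 2. The day-2 ANOVA and the sample size are not affected. This should be fixed before analysis, but it does not threaten the primary test.

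**What to change.** In Plan for statistical analysis:

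- Use only days 1-7 as responses and keep the baseline value as a covariate.
- Add group-by-time.
- Name the day-2 group contrast as the model's estimate for the primary outcome.
- Report the days 3-7 contrast separately, labelled as early versus delayed celecoxib.
- Limit the model to outcomes measured repeatedly. For patient satisfaction and physician evaluation, rely on the single-time tests already planned.

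Adding diagnosis or baseline-by-time is optional and not needed to correct the error. The cost is a few sentences and a few lines of SAS, with no new data and no change to sample size.

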## Discussion

To achieve less postoperative pain, better patient satisfaction, and better rehabilitation after surgery, pain management is very important. Multimodal analgesia for pain management after surgery has been shown effective in controlling postoperative pain [1]. Previously, prophylactic administration of a COX-2 inhibitor, as a multimodal analgesia, has been found to reduce postoperative VAS pain score, opioid analgesic consumption, and active ROM of the knee after TKA surgery [8, 9]. In these studies, a COX-2 inhibitor is administered before surgery.

COX-2 inhibitors and other NSAIDs have only been approved as postoperative, but not as preemptive, analgesia in Japan. In addition, an appropriate fasting period to empty the stomach prior to anesthesia is essential for patient safety, because the risk of inhaling stomach contents into the lungs is reduced. Thus, to verify the effectiveness of administration of a COX-2 inhibitor during the early postoperative period as part of multimodal analgesia, it is necessary to establish clinical practice guidelines. In addition, this method of administration is safe, convenient and general-purpose way in practice. To date, however, no comparative data are available.

This randomized controlled trial design will be used to address the hypothesis, that immediate administration of oral celecoxib after TKA surgery provides superior postoperative analgesia when compared with delayed administration.

The primary outcome of this study is to evaluate the effects of celecoxib administration immediately after surgery on postoperative pain after TKA. Possible benefits of celecoxib include its ease of administration, safety after surgery, its effectiveness and reduction of postoperative opioid consumption. Thus, this study might to identify the influence of immediate administration of oral celecoxib after TKA surgery. This will help to provide clinical management status for patients with TKA surgery.

Opioid consumption for the secondary outcomes will be determined. Opioid is useful and effective for postsurgical pain control. However, the incidence rates of postoperative nausea and vomiting as its side effects could be increased with large amounts of opioid. By taking medicine for pain relief after the early post-operative period, opioid consumption and its side effects could be reduced. As its other expectations, pain relief after surgery might improve the quality of sleep. When postoperative pain is reduced, the range of knee motion with accelerated physical recovery might be improved. Pain relief, good quality of sleep and early functional recovery could improve satisfaction of patients. These will be very important to establish clinical practice guidelines.

The limitation of this study is an open label. However our data will come from patient-reported outcomes and participants will not be affected by any other. Patient–reported outcome will help to understand practical patients’ condition. Therefore, we believe that this study will provide some insight into perioperative multimodal analgesia, which helps to improve perioperative clinical practice.

### Clinical relevance and importance

This randomized controlled trial will help to provide insight to optimize perioperative pain management strategies by evaluating the effect of immediately postoperative administration of analgesics for patient after TKA surgery. These results could improve clinical practice for perioperative pain management and also might help to improve patient satisfaction.

## Trial status

Patient recruitment started in October 2014. The predicted study completion date is March 2016.

## Abbreviations

COX: cyclooxygenase
NSAIDS: nonsteroidal anti-inflammatory drugs
OA: osteoarthritis
PCA: patient-controlled analgesia
RA: rheumatoid arthritis
TKA: total knee arthroplasty
VAS: visual analog scale
